## Methods

3

### Recruitment of target sample

3.1

Participants will be recruited through flyers posted in the community and in local clinics, UCLA data registries, and social media advertisements targeting individuals in the general Los Angeles County (including Ventura, Orange County, Riverside). The target sample for this study will be 160 treatment-seeking depressed male and female adolescents of all ethnicities ages 14–21 years old.

### Study eligibility

3.2

Inclusion criteria includes meeting DSM-V criteria for a depressive disorder, post-pubertal status (Tanner stage ≥3) as determined through self-report Tanner staging (Tanner and Whitehouse, 1976), and starting treatment with either fluoxetine or escitalopram by a clinician. For those under age 18, participants must have a parent/legal guardian who is able to answer questions about family history of mental disorders and the child's behavioral symptoms. All participants and guardian(s) must be able and willing to provide written informed assent and consent, respectively, and able to understand all study procedures (e.g., fluency in English). Exclusion criteria includes a primary Axis I disorder based on DSM-V criteria besides depression (comorbid anxiety diagnosis is allowable), meeting criteria for mania, psychosis, or substance use disorders, stimulant usage, use of antidepressants or other central nervous system medications within five half-lives, a mild concussion within the previous six weeks or severe concussion in the individual's lifetime, evidence of severe psychiatric symptoms requiring hospitalization, first-degree relative with suspected past or present diagnosis of bipolar disorder or schizophrenia, and previous diagnosis of any major illness (e.g., childhood cancer, multiple sclerosis), neurological disorder (e.g., seizures), pervasive developmental disorders, or inflammatory conditions that might interfere with the goals and measures of the study. Any contraindication to MRI scanning (e.g., orthodontics/braces, non-removable piercings, pregnancy), venipuncture (e.g., hematoma, history of trypanophobia, vasovagal reactions to venipuncture), or current SSRI treatment is also exclusionary.

### Study design

3.3

160 treatment-seeking depressed adolescents who meet includion criteria will complete study procedures every 3 months for 18 months (7 timepoints total). The first assessments of this 18-month study capture the pre-SSRI period (T1) and after 12 weeks of the SSRI (T2). Both T1 and T2 will consist of two distinct visits (Visit 1, V1, and Visit 2, V2), spaced approximately 1–2 weeks apart (see Fig. 1). At V1, we will administer clinical interviews (and at T1V1 we will determine final study eligibility as we will review exclusionary criteria) and self-report surveys to capture symptomatology and clinical history including treatment information (this is relevant mostly at T1). At V2, we will assess peripheral measures of pro-inflammatory cytokines and glutamate in fronto-cingulate-limbic circuits utilizing ultra-high field imaging with a 7T MR scanner before and after a social stress paradigm. Finally, every 12 weeks thereafter through 18 months (T3 to T7), we will administer brief clinical interviews and self-report surveys in order to collect information on depression symptoms and diagnosis in order to characterize, and identify predictors of, trajectories of depression.

**Fig. 1 fig1:**
[figure not shown]
**Study design for TIGER.** TIGER will be an 18-month longitudinal study consisting of seven timepoints, each 12 weeks apart. The first two timepoints (T1, pre-SSRI treatment, and T2, post-SSRI treatment) will consist of two visits each: visit 1 (V1) will comprise clinical evaluations and self-report questionnaires and visit 2 (V2) will consist of multimodal neuroimaging (see Table 1) and biospecimen collection. After T2, participants will complete five follow-up assessments every 12 weeks (T3-T7), which will consist of clinical assessments of depression, updated treatment and health history information, and completion of self-report questionnaires.

The rationale for the intervals in our study design are as follows: as the vast majority of depressed adolescents seen in the clinics we will be recruiting from will be treated with antidepressants for the first time, we will minimize heterogeneity in antidepressant treatment at study enrollment by only including those who will be initially treated with fluoxetine or escitalopram. The clinical recommendations for treating depressed adolescents with SSRIs are to start with a low dose to minimize potential side effects and then to increase the dose as quickly as tolerated by the patient to reach a therapeutic dose based upon FDA guidelines; if the patient does not respond after 4–6 weeks at a given dose, the recommendation is to gradually increase this dose to the maximum dose approved by FDA guidelines that can be safely tolerated. If the patient does not improve even after being at the FDA-approved maximal dose for at least 6 weeks, the recommendation is to switch to another SSRI. Due to these clinical practice parameters, we anticipate and expect virtually all participants to be on an SSRI (and, specifically, fluoxetine or escitalopram for at least 6 months of the study). However, we also expect and anticipate that doses will be reduced or augmented at any time at the direction of the treating clinician; we will account for these dose changes and differences statistically as covariates. After T2, participants may not necessarily remain on SSRIs and are likely to undergo various changes in treatment, particularly for the TNR group. Regardless, we will collect clinical information regarding history of medication usage at T1 and current medication usage (and psychotherapies) every 12 weeks from both the child and parent throughout the study, including assessment of adherence to medication, switching medications or to other antidepressant classes, and reasons for any medication changes (e.g., side effects, cost). Maintaining consistent intervals between assessments will thereby facilitate longitudinal analyses.

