## Study aims & hypotheses

2

In Aim 1, we will establish whether psychosocial stress increases levels of peripheral inflammation and levels of glutamate in fronto-cingulate-limbic circuits in adolescents with depression.

In Aim 2, we will define TNR based on whether depressed adolescents exhibit at least a 50% reduction in CDRS-R scores after 12 weeks of SSRI treatment. We will compare TNR versus non-TNR groups on TSST-related changes to inflammatory cytokines and glutamate. We will also test whether TSST-related changes in glutamate before and after SSRI treatment mediate the associations between TSST-changes in cytokines at baseline and TNR status (binary outcome). We will also explore models using depression severity as dimensional outcomes instead. We hypothesize that compared to non-responders, responders will show greater stress-induced increases in cytokines and glutamate, as well as stronger positive associations between cytokines and glutamate in threat neurocircuitry.

In Aim 3, we will characterize 18-month trajectories in adolescent depression from behavioral, inflammatory, and neural indicators of threat to social stress. Seven repeated clinical assessments over 18 months will support identifying depression trajectory subgroups (e.g., persistent depression, gradual remission, etc). For binary outcomes (diagnosis of depression), we will use information from clinical interviews to determine remission, relapse, or recurrence status at each timepoint. For dimensional outcomes, we will use symptom severity scores. We hypothesize that increased levels in indicators of sustained threat before and after SSRI treatment, as well as severity of past and ongoing life stress, will predict increased likelihood of experiencing chronic and unremitting depression over 18 months.

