For all of the statistical analyses testing these hypotheses, potential demographic (e.g., age, gender), clinical (e.g., age of depression onset, number of comorbidities, presence of childhood trauma), or biological (e.g., percentage of gray matter in MRS voxel) covariates will be included if they are correlated with our outcome variables*.* Statistical significance will be set at α = 0.05. We will apply false discovery rate (FDR) correction as appropriate. In all simulation analyses for estimating sample size based on 1-β = 0.8, effect sizes (*r* or η2 or mean ± SD) were based on preliminary data or cited literature. For the hypotheses in Aims 2 and 3 that require logistic ridge regression analysis, we plan to sample 90% data as the training set and 10% as the testing set across 10 iterations; power was therefore calculated based on 90% of the sample after accounting for attrition (*N* = 108). We will put in rigorous effort to minimize missing data, including scheduling sessions around families’ availability, repeating scans when data were not useable due to movement or scan/user error, and providing bonus incentives for completing all follow-up assessments. For all longitudinal analyses, we will use flexible modeling approaches that allow individuals who provide at least one assessment to be included in our estimation of the effects of interests.

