One challenge we anticipate is that we will have an unknown distribution of patients who will be TNR at T2. For our power analyses, we have estimated that 40% of the sample will be considered TNR after 12 weeks of SSRIs based on prior clinical trials. Furthermore, due to clinical practice paramters, FDA guidelines, and patient response, we also expect and anticipate that SSRI doses will be reduced or augmented at any time during the study at the direction of the treating clinician. Regardless, we will collect clinical information regarding history of medication usage, current medication usage (including psychotherapies) every 3 months throughout the study, as well as assess adherence to medication, switching medications or to other antidepressant classes, and reasons for any medication changes (e.g., side effects, cost). We will account for these dose changes and differences statistically as covariates in our analyses. Also, we will acquire data on depression symptom severity (i.e., CDRS-R, PHQ-9) and will be able to use a *dimensional* measure of depression symptom changes as an outcome in our statistical models. Another potential challenge we will face involves the timing of biospecimen collection: we aim to collect the post-TSST blood sample to measure inflammatory markers 120 minutes post stress-onset to capture acute stress responses, but we may be missing stress reactivity windows for some participants by only obtaining one post-stress sample. We will use time of collection as a covariate for this study but future work may benefit from the collection of multiple post-stress blood samples. Finally, this study employs stress induction through the TSST, but future work should also mechanistically investigate stress *reduction* paradigms to examine how lowering stress may acutely impact peripheral inflammation and glutamate metabolism in depressed adolescents.

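### Dose changes driven by early response are to be covariates, so models of baseline biomarkers predicting non-response condition on part of the response process

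*Protocol article*

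**What the plan says.** The rule appears twice in the protocol article. Section 3.3 (Study design) says "we will account for these dose changes and differences statistically as covariates". Section 5 (Discussion) says "We will account for these dose changes and differences statistically as covariates in our analyses". Neither statement is limited to an aim, a model or a sensitivity analysis.

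The article also says why doses move. In section 3.3, "if the patient does not respond after 4–6 weeks at a given dose, the recommendation is to gradually increase this dose", and a change of drug is considered "If the patient does not improve even after being at the FDA-approved maximal dose for at least 6 weeks". The Discussion names response again: "due to clinical practice paramters, FDA guidelines, and patient response, we also expect and anticipate that SSRI doses will be reduced or augmented". After T2, participants "are likely to undergo various changes in treatment, particularly for the TNR group".

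The Aim 2 outcome (section 2) turns on "at least a 50% reduction in CDRS-R scores after 12 weeks of SSRI treatment". The general rule in the same section is that "covariates will be included if they are correlated with our outcome variables".

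**The concern.** TNR is scored at week 12. A dose increase prompted by lack of response at weeks 4–6 comes after the T1 biomarker and before TNR, and it carries information about how response is developing. If a T1 biomarker predicts TNR through early response, holding dose change fixed removes part of the association that Aim 2 is meant to find. If other, unmeasured causes also drive early response, conditioning on dose change links them to the biomarker and can distort the estimate either way. For Aim 3, doses after T2 can follow earlier severity in the same manner.

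The general covariate rule gives no protection, because a response-driven dose change will correlate with the outcome almost by construction and so will qualify for inclusion. At stake are the main Aim 2 comparison of baseline biomarkers and the Aim 3 predictor effects, in a study with few TNR cases.

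**Working it through.** **1. Order of events.** T1 biomarker → response at weeks 4–6 → dose increase if there is no response (section 3.3) → TNR at week 12 (section 2). Dose change lies after baseline and is affected by the developing outcome. It is not affected by TNR status itself, which is fixed later.

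**2. Sample size.** Section 2 gives N = 108 as 90% of the sample after attrition, so 108 / 0.9 = 120 completers. Against the 160 enrolled this implies attrition of 1 − 120/160 = 25%; the article states no rate. At the Discussion's 40% TNR, 0.4 × 120 = 48 cases. No effect size is given, so the stated power of 0.80 cannot be reproduced. The simulations below illustrate the mechanism and do not check a stated figure.

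**3. Simulation inputs.** From the article: 40% TNR and α = 0.05 (taken as two-sided). N = 120 is derived above. Everything else is assumed. X is the standardised T1 biomarker, L6 and L12 are latent improvement at weeks 6 and 12, and D = 1 for a dose increase. D has one probability in the poorer half on L6 (early non-responders) and another in the better half. TNR is the lowest 40% of L12. The logistic model of TNR on X is fitted with and without D, and shrinkage = 1 − (log-odds with D) / (log-odds without D).

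- Model A (biomarker acts only through early response): L6 = 0.3X + √(1 − 0.09)·u; L12 = c·L6 + √(1 − c²)·v + δD; c = 0.6 or 0.8; δ = 0 or 0.3 SD.
- Model B (biomarker has its own effect on both early and late response): effect 0.3 on each; residual correlation 0.4–0.8; δ = 0 or 0.3 SD.

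| Dose increase, early non-responders / responders | Shrinkage, A | Shrinkage, B | A with c = 0.8, δ = 0: log-odds without → with D | Power at n = 120 |
|---|---|---|---|---|
| 50% / 50% | none (−2 to 0%) | none | −0.408 → −0.408 | 0.53 → 0.53 |
| 70% / 30% | 2–8% | about 0–4% | −0.398 → −0.373 | 0.57 → 0.49 |
| 80% / 20% | 11–19% | 2–10% | −0.403 → −0.341 | 0.54 → 0.37 |
| 90% / 10% | 26–35% | 6–20% | −0.399 → −0.273 | 0.54 → 0.22 |
| 100% / 0% | not run | 13–37% | – | – |

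Worked example at 80% / 20%: 1 − 0.341/0.403 = 15%. At 90% / 10%: 1 − 0.273/0.399 = 32%. When dose is unrelated to early response nothing is lost, so the loss comes from the mechanism that section 3.3 describes.

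**4. Direction.** Let X affect only whether a dose increase happens (for example through tolerance) and not response: logit P(D) = −2·L6 + gX, c = 0.8, no dose effect. The rejection rate at nominal 0.05 with n = 120 is 0.049 without D and 0.098 with D at g = 0.5, and 0.046 and 0.238 at g = 1.0. Adjustment can therefore create an association as well as hide one.

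**5. Measures taken at T2.** Section 2 also uses glutamate changes after SSRI treatment as mediators of TNR. Let a T2 measure be raised 0.5 SD by a dose increase but be unrelated to response, with n = 120. The false-positive rate is 12.7% without D and 5.7% with D at 90% / 10%, and 8.4% and 4.9% at 80% / 20%. Across the assumptions tried, leaving dose out gives about 6–14%. Here dose acts as a confounder, and omitting it does harm.

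**6. Aim 3.** This was not simulated, because the article gives no model form. The point there rests on the same ordering of events.

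**The case against.** The strongest case against has four parts.

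- **Many dose changes are not driven by response.** Section 3.3 describes a low start with increases as tolerated, changes at any time, and reasons such as side effects and cost. This stands. It is why the size is a range that starts near zero.
- **Dose may itself cause response.** The Introduction ties TNR to an adequate trial at a therapeutic dose, so some patients scored as TNR may have been under-dosed. Wanting to allow for dose is legitimate and is partly a choice of estimand. But an ordinary covariate cannot separate dose as a cause of response from dose as a result of non-response.
- **Dose belongs in analyses of T2 measures.** This stands (step 5) and limits the fix.
- **The unseen analysis plan may narrow the rule.** It may. But the article states the rule twice without restriction, and it uses the sensitivity label elsewhere: for mood ratings in section 3.6, and for time since wakening, collection time and BMI in section 3.7. Dose carries no such label.

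A reader might infer more than the text supports. The article does not say that drug switches or other treatment changes after T2 will be covariates. It says only that such information will be collected, and the adjustment sentence concerns dose. Nor is an increase at weeks 4–6 a consequence of TNR itself; it follows early response.

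**Conclusion.** The point holds for models in which a T1 biomarker predicts 12-week TNR or the 18-month course. Followed as written, the rule conditions on a post-baseline variable that the article itself says is driven partly by response. The usual effect is a weaker biomarker association and lower power; bias in the other direction is possible.

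No stated figure is shown to be wrong. The size is unknown because the article gives no escalation rates. Under the assumptions shown, Aim 2 shrinkage runs from about nil at 70% / 30% to 13–37% at 100% / 0% in model B, and from 2–8% at 70% / 30% to 26–35% at 90% / 10% in model A. For Aim 3 the size has not been estimated.

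Two stronger conclusions are tempting and not supported. One takes the all-or-nothing case as the expected loss; it requires every early non-responder and nobody else to have a dose increase, which does not fit the other reasons for dose change that the article lists. The other is that dose should leave every Aim 2 and Aim 3 model; for T2 measures that would replace one bias with another.

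**What to change.** - **Primary Aim 2 and Aim 3 models of T1 predictors:** state that they adjust only for pre-treatment variables, for example the SSRI prescribed at T1 and baseline CDRS-R, and exempt post-baseline dose from the correlated-with-outcome rule.
- **Dose-adjusted version:** report it as a labelled sensitivity analysis, preferably by inverse-probability weighting or another g-method that uses the reasons for medication change the study already plans to record.
- **Measures taken at T2, including post-SSRI glutamate as a mediator:** keep dose in the analysis, and name a method suited to treatment affected by earlier response.

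The cost is analysis wording, with no new data and no effect on how doses are managed. The downside is that the primary estimate describes prognosis under clinician-directed titration and not at a fixed dose, and the text should say so. The change should be made before the outcome data are analysed.

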### Measures of depression

3.4

We will be administering the K-SADS-PL (Kaufman et al., 1997) for assessing Axis I disorders in all study participants (as assessments for depressive disorders do not meaningfully differ between K-SADS-PL and similar instruments designed for adults such as the Structured Clinical Interview for DSM Disorders). The K-SADS-PL will be used at baseline to determine depression diagnosis according to the DSM-5 and study eligibility (as potential participants with a history of mania, psychosis or who have current substance use disorders will be excluded from the study). Depression diagnosis will also be used as an outcome measure to determine remission versus recurrence throughout the study period. We will also administer a modified version of the Family Interview for Genetic Studies (FIGS; Maxwell, 1992) at T1 in order to exclude potentially depressed participants who have first-degree relatives with mania or psychosis. The study group will convene weekly to discuss any ambiguous codes.

To assess depression severity dimensionally, we will administer the Children's Depression Rating Scale-Revised (CDRS-R), a 17-question, clinician-rated scale assessing dimensional scores of depression severity, and the Reynolds Adolescent Depression Scale, 2nd Edition (RADS-2), which is a 30-item self-report questionnaire assessing depression severity for the past two weeks. Both scales have been widely used in clinical trials and research studies of adolescent depression demonstrate sensitivity and reliability in assessing depression symptoms across time (Poznanski et al., 1984; Reynolds, 2010). Additionally, we will administer the Patient Health Questionnaire 9 (PHQ-9), a 9-item screener for depression that is commonly used in clinic and research settings for adults and adolescents and for assessing rapid symptom changes (Kroenke et al., 2001).

### Other clinical and self-report measures

3.5

To support exploratory hypotheses and collect collateral information on factors that relate to and/or influence depression and inflammation, we will be administering additional instruments and questionnaires. Specifically, to examine anxiety symptoms, we will administer the Multidimensional Anxiety Scale for Children (MASC-2), a 39-item questionnaire assessing anxiety symptoms (March et al., 1997), and the Generalized Anxiety Disorder-7 (GAD-7), a 7-item screener for generalized anxiety disorder that is commonly used in both clinic and resarch settings for adults and adolescents (Spitzer et al., 2006). Suicidal and other self-injurious thoughts and behaviors will be assessed using common instruments in the field for this population, including the Suicidal Ideation Questionnaire (SIQ (Reynolds, 1987)), the Columbia Suicide Severity Rating Scale (C-SSRS; (Posner et al., 2011), and the Self-Injurious Thoughts and Behaviors Interview (SITBI (Nock et al., 2007)). We will also collect information on stress exposure, including current levels of stress using the Perceived Stress Scale (PSS (Cohen et al., 1983)), lifetime exposure to adversity using the Stress and Adversity Inventory for Adolescents (Slavich et al., 2019), experiences of discrimination using the Adolescent Discrimination Distress Index (Fisher et al., 2000), and emotion regulation tendencies using the Difficulties in Emotion Regulation Scale (Gratz and Roemer, 2004).

### Trier Social Stress Task (TSST)

3.6

A modified version of the Trier Social Stress Task (TSST) will be administered at T1V2 and T2V2. This adapted TSST involves no deception and follows procedures similar to those used by our group in adolescent populations (Ho et al., 2020; Kircanski et al., 2019; Miller et al., 2019). Following the first set of brain imaging acquisitions and the first blood sample collection, participants will be instructed by an experimenter that they will be completing a stress test. There will be two versions of the stress test: a five-minute arithmetic task or a five-minute speech task (regardless of the task, participants will be given 5 minutes of prep time beforehand). Participants will be randomly assigned one of the two stress tests at T1 and will be administered the second stress test at T2 to minimize habituation with repeated testing and ensuring that the order of the two tests are counterbalanced across the sample.

Upon arrival to the session, before, and after the TSST, participants will provide ratings of ten mood states (*Excited, Afraid, Confused, Sad, Energetic, Angry, Happy, Tired, Tense)* based on the Positive and Negative Affect Schedule (PANAS; Crook et al., 1998) on a visual analogue scale from 0 to 10. These ratings will be used as tertiary outcome measures of behavioral responses to social stress. During administration of the TSST, we will also collect saliva samples repeatedly to explore changes in stress hormones before and after an acute stressor. Five saliva samples, each collected approximately 10 minutes apart, will be collected using the SalivaBio Oral Swab Method (Salimetrics, LLC) during the TSST protocol, from which we plan to assay cortisol production. After completing the TSST, participants will complete the remaining scans and provide a secondary blood sample approximately 120 minutes after the first blood sample and then provide a final saliva sample. Additionally, it is possible that secondary stress and anxiety may affect cytokine and CRP levels at Time 1, as this will be the first time most of the participants will have undergone an MRI scan; however, our primary measures of inflammation and glutamate are *within-person differences* before and after the TSST. We will also consider using the PANAS ratings of mood states as covariates in sensitivity analyses.

